**Figure 2 fig2:**
[figure not shown]
Hierarchy of clinical composite score. NYHA = New York Heart Association classification; PGA = Patient Global Assessment.

In the BIO-AffectDX study, subjects will be analyzed on both an intention-to-treat and an as-treated basis to account for removal or exchange of the implanted CRT-DX device system. The primary analysis for the primary objective will include the entire cohort, including all AF subtypes. Secondary objective analysis for each AF subtype (ie, paroxysmal AF, persistent AF, and long-standing persistent AF) subgroup will utilize the subtype documented at the baseline medical history collection using the intention-to-treat population.

Several prespecified and preplanned exploratory subgroup analyses on primary and secondary objective data will also be performed, when it is determined feasible and appropriate based on the available data The prespecified subgroups may include, but are not limited to, the following: AF subtype, AF burden, age, sex, race, NYHA class, LV ejection fraction, type of cardiomyopathy, QRS type and duration, ablation type and status, LV lead position and pacing vector, DX lead tip position in addition to the atrial dipole position (based upon operator visual assessment as high atrium, mid atrium, low atrium, or other), number of hospitalizations within the last 12 months, number of HF or arrhythmia hospitalizations within the last 12 months, ventricular pacing percentage, left atrial size and LV dimensions obtained during baseline echocardiography, degree of mitral regurgitation, and clinically relevant echocardiographic data. Additionally, study objective outcomes may be compared to rates from published literature and/or outcomes from a contemporary control group of subjects in sinus rhythm receiving a CRT-D. Daily remote monitoring data, including but not limited to AF burden and ventricular arrhythmias, will be obtained throughout the study participation. A variety of analyses will be conducted on the subgroups depending on the structure of the data and given normality. For categorical data this includes χ^2^, binomial proportion test, and McNemar test, while for continuous data includes paired *t* test, *t* test, and 2-sample *t* test. If the assumption of normality is not met, then nonparametric versions of the appropriate method will be used. Effect sizes and 95% confidence intervals will be given for all results of the subanalyses. An alpha of 0.05 will be used, and all analysis will be conducted with SAS 9.4 (SAS Institute Inc, Cary, NC).

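### Continuous baseline factors are listed as exploratory subgroups and no method for a continuous predictor is named; cutting them, the natural reading, would lose about 36% of the information at a median split.

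*Protocol article*

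**What the plan says.** The relevant text is in the protocol article, Data analysis, in the paragraph on exploratory subgroups.

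- **Factors.** The subgroup list includes "age, sex, race, NYHA class, LV ejection fraction, type of cardiomyopathy, QRS type and duration" and "left atrial size and LV dimensions obtained during baseline echocardiography". Age, LV ejection fraction, QRS duration, left atrial size and LV dimensions are all measured on a continuous scale. No cut-points are given. The list is open: "The prespecified subgroups may include, but are not limited to, the following".
- **Outcomes.** The subgroup analyses cover the primary and the secondary objectives. The secondary objectives (Objectives section) include changes in the two quality-of-life questionnaires (AFEQT and MLHFQ), the 6-minute walk test and AF burden, all of them continuous. The CCS itself has three levels.
- **Methods.** "A variety of analyses will be conducted on the subgroups depending on the structure of the data and given normality". Besides chi-square, the named methods are "binomial proportion test, and McNemar test, while for continuous data includes paired *t* test, *t* test, and 2-sample *t* test", with nonparametric counterparts if normality fails. The significance level is stated: "An alpha of 0.05 will be used". Effect sizes with 95% confidence intervals are promised for every subanalysis.
- **Status.** Sample size justification calls the secondary analyses and subanalyses exploratory and not adequately powered. General considerations calls the study results hypothesis generating.

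**The concern.** Every named test is a one-sample, paired, two-group or contingency-table test. Applied to subgroups of age or ejection fraction, these tests need the factor to be cut. Subjects just either side of a cut are then treated as different, and all subjects within a group as alike. This lowers power, hides the shape of the relation and makes the answer depend on where the cut falls.

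The subanalyses are already described as underpowered, so a further loss that can be avoided with the data in hand is worth removing. The stake is limited to the exploratory question of which patients with AF and HF improve after CRT.

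**Working it through.** The article gives no figure for these analyses, so there is none to reproduce. The check has three parts.

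**1. Can the named tests use the factor uncut?**

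| Outcome | Named test that uses the uncut factor | What it yields |
|---|---|---|
| CCS, improved vs not improved | 2-sample t test of the factor between the two outcome groups | A difference in mean age, ejection fraction, etc.; not the effect on improvement per unit of the factor |
| CCS, three levels | None unless the levels are collapsed to two | As above |
| AFEQT, MLHFQ, 6-minute walk or AF burden change | None; either the factor or the outcome must be cut | – |

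**2. Information kept after a cut.**

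Inputs: a standard normal factor, a linear effect and a cut at quantile q (all assumed); n = 400 (Sample size justification).

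The efficiency of a two-group split relative to a linear term is the squared correlation between the factor and its split indicator:

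E = φ(c)² / [q(1 − q)], where c is the normal quantile of q.

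- Median: c = 0, φ = 0.3989, so E = 0.1592 / 0.25 = 0.637 (= 2/π). Loss 36.3%; 400 × 0.637 ≈ 255 effective subjects.
- 25/75: c = 0.674, φ = 0.3178, so E = 0.1010 / 0.1875 = 0.539. Loss 46.1%; 400 × 0.539 ≈ 215 effective subjects.
- 80/20: E = 0.490. Loss 51.0%.
- Tertiles: loss 20.7%. Quartiles: loss 13.9%.
- Uniform rather than normal factor, median split: loss 25%.

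**3. Power.**

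Inputs: α = 0.05 (stated; two-sided assumed), n = 400, improvement rate p of 50% to 70% (assumed). The effect is set for 80% power on the continuous scale: log OR per SD = (1.96 + 0.8416) / √[400·p(1 − p)].

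- p = 0.5: 2.8016 / 10 = 0.280, OR 1.32
- p = 0.6: 2.8016 / 9.80 = 0.286, OR 1.33
- p = 0.7: 2.8016 / 9.17 = 0.306, OR 1.36

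Analytic power after a split is Φ(2.8016·√E − 1.96):

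- Median: Φ(2.8016 × 0.798 − 1.96) = Φ(0.275) = 0.61
- 25/75: Φ(2.8016 × 0.734 − 1.96) = Φ(0.096) = 0.54

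Simulation, 2000 runs per row:

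| Assumed p | OR per SD | Chi-square, median split | 2-sample t, factor uncut | Logistic, factor continuous |
|---|---|---|---|---|
| 0.5 | 1.32 | 0.58 | 0.78 | 0.78 |
| 0.6 | 1.33 | 0.60 | 0.80 | 0.80 |
| 0.7 | 1.36 | 0.59 | 0.77 | 0.77 |

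More groups do not recover the power of an overall test. Tertiles and quartiles keep more information but spend 2 and 3 degrees of freedom. At the same effect, power is 61% for two groups, 60% for tertiles and 57% for quartiles.

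**The case against.** The strongest reply is that the text does not require a cut. Both lists are open, the choice of analysis is left to the structure of the data, and the article nowhere says that regression will not be used. Cut-points and model forms for exploratory analyses are commonly left to the full protocol or analysis plan, which are not shown. In addition, a named test, the 2-sample t test of the uncut factor between improved and not-improved subjects, performs as well as logistic regression in the table above.

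Much of this stands. Three stronger readings are tempting and should not be drawn:

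- **That these factors will be analysed only as cut groups, or must be cut.** The open wording does not support *only* or *must*. It supports the statement that no method for a continuous predictor is named and that cutting is the natural reading of tests conducted on subgroups.
- **That the plan loses a third of its information.** The 36% belongs to a median split of a normal factor with a linear effect. The plan fixes no cut, and the normal-factor figure does not carry over to counts such as prior hospitalizations.
- **That false-positive rates are inflated.** Picking the cut from the data would raise the type I error of a 5% test to roughly a third in simulation. The plan does not propose this; it describes the subgroups as prespecified.

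The reply does not dispose of the point. The article states a family of methods, so this is more than silence. For a continuous outcome against a continuous factor, that family contains no test that works without a cut. For the CCS, the reversed t test does not give the effect on improvement that a reader would want beside a promised effect size and interval.

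**Conclusion.** The concern holds in a limited form: the named tests fit the continuous subgroup factors badly, although the wording leaves room for better ones. If the factors are cut, the cost is about 36% of the information at the median and about 46% at 25/75, and power falls from about 80% to about 60% after a median split. These figures assume a normal factor, a linear effect, a two-sided 5% test, 400 subjects and an improvement rate of 50% to 70%. Baseline echocardiographic factors are collected only where available, so their absolute power will be lower whichever analysis is used.

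The primary estimate is unaffected, and so is the comparison by AF subtype, which is categorical. This is a minor, inexpensive improvement to exploratory analyses, not an error that threatens the study's conclusions.

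**What to change.** In Data analysis, after the list of subgroup tests, state that:

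- continuous baseline factors will be analysed by regression on the measured value: logistic or proportional-odds for the CCS, linear for change scores;
- each model will include a simple non-linearity check, such as a quadratic term or a restricted cubic spline;
- the effect will be reported per clinically sized unit of the factor, with its 95% CI;
- any categorical subgroup display will use fixed cut-points specified in advance.

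The cost is a few more models in SAS 9.4, the software already named, and a per-unit effect or a plot in place of a two-row table. No new data and no change to study conduct are needed.

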## Significance of the trial

The BIO-AffectDX study will provide important clinical information regarding improvement in clinical outcomes in patients with HF and AF who receive a CRT-D device. There are several knowledge deficits in the space targeted by the BIO-AffectDX study. First, since many prospective clinical trials investigating improvement of patients receiving CRT-D excluded patients with AF, the BIO-AffectDX study will evaluate the overall improvement of a CCS of HF in patients that have been identified as having evidence gaps related to the effectiveness of CRT, namely those with coexisting AF and HF. Patients enrolled in the BIO-AffectDX study will all have a history of AF. All subtypes of AF will be enrolled, including paroxysmal, persistent, and long-standing persistent AF. Given the exclusion of AF patients in many CRT trials, the BIO-AffectDX study will be one of the largest prospective studies to ever study clinical outcomes in this unique population. Second, additional secondary outcomes in patients with AF and congestive heart failure receiving CRT-D therapy will be evaluated in the BIO-AffectDX study, including quality of life, HF hospitalization, death, and maintenance of sinus rhythm. Therefore, the BIO-AffectDX study will be able to specifically analyze several clinical outcomes in this population of patients, and evaluate differences based on the patient subtype of AF. Third, the BIO-AffectDX will utilize a unique CRT-D system that does not require implantation of a separate atrial lead, but utilizes an atrial dipole contained within the high-voltage defibrillator lead for atrial sensing. The study allows for the evaluation of outcomes in patients with AF and HF that qualify for CRT-D therapy with the use of fewer leads to provide this CRT therapy and will provide important insights into outcomes in AF patients who qualify for CRT therapy but may not require atrial pacing therapy.

The authors anticipate that the results of this important study will inform future societal consensus and guideline documents that call for further study of the effect of CRT in AF patients, and will help clarify the role of CRT therapy in patients with both AF and HF that qualify for CRT therapy use.

## Patient Consent

Written informed consent will be obtained from the patient prior to collecting any study-specific data.

## Ethics Statement

Institutional Review Board approval is required from each institution prior to participation in this clinical study.
